## Abstract

**Objectives:**

Non-invasive brain stimulation has emerged as a safe, pain-free, and cost-effective method for post-stroke aphasia (PSA) rehabilitation. However, the ideal site for stimulation is yet to be determined. The cerebellum has demonstrated its role in language function though the application of repetitive transcranial magnetic stimulation (rTMS) targeting the cerebellum for PSA has not been well-documented. This study aims to assess the short- and long-term efficacy of rTMS on the right cerebellum in enhancing language recovery in patients with PSA in the subacute phase, and to explore its neuropsychological and neural network mechanisms as well.

**Methods:**

Our study will recruit sixty-six PSA patients, who will be randomly divided into either a real or a sham rTMS group with equal distribution. The real rTMS group (n  =  33) will receive rTMS treatment over the right cerebellar hemisphere along with speech-language therapy (SLT), while the sham group (n  =  33) will receive sham stimulation and SLT. We will assess the outcomes at five intervals: before rTMS treatment, 2, 12, and 24 weeks, and 1-year post-treatment. The primary outcome in this research is the change in performance of the West Aphasia Battery from baseline to the final follow-up. Secondary outcomes include alterations in the structure, function, and perfusion neuroimaging data, as well as changes in non-verbal cognitive functions, measured using the Loewenstein Occupational Therapy Cognitive Assessment over time and between the groups. Any adverse event related to rTMS therapy will also be recorded. The results of this trial will provide insights into whether cerebellar rTMS stimulation (1) improves language function recovery in subacute phase PSA patients; (2) strengthens the functional connection of the cerebro-cerebellar network, and (3) enhances aphasia treatment outcomes by improving non-linguistic cognitive functions. We commenced patient recruitment for this trial in June 2026, and it is currently in progress.

**Registration** This project was prospectively registered at the Chinese Clinical Trial Registry (ChiCTR2600125453).

## Introduction

Post-stroke aphasia (PSA), often results from brain lesions impacting cortical and subcortical structures, is characterized by difficulties in speech, comprehension, repetition, and naming, leading to extended hospital stays, diminished quality of life, and increased mortality [1]. Currently, the go-to treatment protocol for PSA is speech-language therapy (SLT), which has demonstrated beneficial effects on language function [2–4]. However, not all PSA patients have access to this therapy, and not all benefit from it. Despite SLT, individuals with aphasia frequently experience persistent communication challenges [3,5]. Thus, the development of additional, more effective therapeutic approaches for aphasia treatment is crucial. Researchers are exploring non-invasive brain stimulation (NIBS), a safe, painless, and cost-effective technique, as a potential enhancer for aphasia treatment [6–8]. The combination of NIBS with traditional therapy shows promise in aphasia recovery, as underscored by international guidelines [6,8].

Aphasia rehabilitation often targets the cerebrum, with most research focusing on stimulation of the left hemisphere due to the reactivation and utilization of the residual left-hemisphere tissue in language recovery [6,8–10]. Some studies apply inhibitory stimulation to the right hemisphere, based on the theory of inter-hemispheric disinhibition [11–13]. However, there are limitations to both approaches over the cerebral hemispheres [14]. Stimulating the left cerebral hemisphere can be problematic, as stroke often leaves areas with low electrical resistance due to filled with cerebrospinal fluid. This reduces the stimulation exposure on the targeted tissue [15–16]. Conversely, inhibiting the right hemisphere might also have negative effects, as evidence suggests that it may play a compensatory role in recovering language functions after a stroke [17–18]. Given the variability in lesion location and size, as well as the unpredictable brain reorganization, determining the optimal stimulation strategy at the cortical level is challenging [19]. Hence, it’s crucial to develop novel stimulation protocols targeting other significant areas involved in language processing, thereby improving the effectiveness of PSA treatment.

Recently, the cerebellum has gained attention as a new possible target for aphasia treatment [16,20–22]. Extensive research shows that the right cerebellum significantly contributes to a variety of language functions, such as word retrieval, verbal memory, language learning and semantic processing [23–24]. Apart from that, the cerebellum is generally far from the usual stroke locations linked to aphasia, reducing the chance of electrical current flow being affected by encephalomalacia [16]. Thus, this method works well for patients with cerebrum hemisphere strokes or aphasia related to bilateral brain strokes. Recent clinical studies have indicated that stimulating the right cerebellum with NIBS can enhance speech and language therapy in PSA patients [16,20–22], suggesting the cerebellum as an excellent site for neuromodulation in the management of PSA.

The cerebellum, with its unique plasticity mechanism and extensive connections to cortical areas, holds promise as a potential target for aphasia rehabilitation [25–26]. Cerebellar NIBS can induce cerebellar excitability changes and brain function modulation via the cerebellar-thalamic-cortical loop, as well as supporting the recovery of lost functions through inherent learning processes [27–30]. By enhancing functional connectivity between the right cerebellum and the cerebral cortical areas engaged in language processing, stimulation of the right cerebellum has demonstrated beneficial effects in enhancing SLT for language recovery [31]. Beyond its role in linguistic function, cerebellar NIBS also significantly contributes to other cognitive functions, notably in executive function that is tightly interconnected with language [31]. Our earlier research has underscored the significant correlation between non-linguistic cognitive impairments and language impairments in patients with PSA [32]. Thus, it is plausible to deduce that cerebellar stimulation could provide therapeutic benefits in aphasia by enhancing their non-linguistic cognitive functions, an aspect which remains unexplored in prior studies.

The majority of prior research, however, has focused on chronic stroke phase aphasia patients whose functional brain structures have already undergone irreversible alterations [4,33,34]. This could potentially explain the observed lack of significant effects of cerebellar NIBS on language recovery [22,35]. Recent guidelines indicate the safe and tolerable application of NIBS even in the sub-acute phase, with no severe adverse effects reported [36–39]. The current study protocol proposes to stimulate the right cerebellum with repetitive transcranial magnetic stimulation (rTMS) in order to enhance SLT for PSA patients in the sub-acute phase. The study’s primary objective is to assess the short- and long-term efficacy of cerebellar rTMS for aphasia recovery in these patients under a randomized, sham-controlled design. The secondary purpose is to examine alterations in functional connectivity between the cerebellum and language-related cortical regions pre- and post-treatment and elucidate the neural restructuring mechanism. Moreover, from a neuropsychological perspective, the study will investigate whether cerebellar stimulation can improve language symptoms through enhancing non-linguistic cognitive functions.

## Methods

### Study design

This is a randomized, double-blinded, sham-controlled and single-center clinical study (Registry: Chinese Clinical Trial Registry; Registration number: ChiCTR2600125453). Patient with PSA will be recruited and will be randomized 1:1 into two groups: the sham and real stimulation group. Patient in the real stimulation group will receive rTMS targeting the right cerebellum, as well as conventional language rehabilitation training. While the sham stimulation will be implemented in the sham group. Language and cognitive function evaluation and neuroimaging data will be collected before rTMS treatment (T0) and at 2 weeks (T1), 3 months (T2), 6 months (T3), and 1 year (T4) after treatment (Please see more details in Fig 1 and Fig 2). The trial protocol conforms to the Standard Protocol Items: Recommendations for Interventional Trials (SPIRIT) Checklist (S1 Checklist) [40]. All participants have provided signed informed consent (S2 File). The study will adhere to the guidelines set forth in the Declaration of Helsinki.

**Fig 1 pone.0354837.g001:**
[figure not shown]
SPIRIT schedule. Abbreviation: WAB: West Aphasia Battery; MRI: Magnetic Resonance Imaging; LOTCA: The Loewenstein Occupational Therapy Cognitive Assessment; TMS: Transcranial Magnetic Stimulation; VAS: Visual Analog Scale; FSAS: Fatigue Self-Assessment Scale.

**Fig 2 pone.0354837.g002:**
[figure not shown]
The flow chart of the study. Abbreviation: PSA: post-stroke aphasia; WAB: West Aphasia Battery; LOTCA: The Loewenstein Occupational Therapy Cognitive Assessment; rTMS: repetitive transcranial magnetic stimulation; VAS: Visual Analog Scale; FSAS: Fatigue Self-Assessment Scale.

### Recruitment

Participants were recruited in the department of neurology and rehabilitation in Beijing Tiantan Hospital. Patients will be recruited for the trial through leaflet distribution and posting recruitment information on the bulletin board. Participation is voluntary, and individuals will have a complete understanding of the trial’s details before enrolling. The attending physician will collect data on medical history, neuroimaging, and scale assessment results.

### Eligibility criteria

#### Inclusion criteria.

To be eligible for the study, participants must be 18 years or older, right-handed, modern standard Chinese Mandarin-speaking (primary language), with more than 6 years of educational level. The study will collect first-onset stroke aphasia patients with the National Institute of Health stroke scale (NIHSS) score ≤ 3 and the lesion located in the left cerebral hemisphere. Patients will be diagnosed according to current clinical diagnostic criteria of ischemic stroke based on informant report, neurological examination, and brain neuroimaging [41]. And aphasia will be diagnosed by the western aphasia battery (WAB) with the standard of aphasia quotient (AQ)< 93.8 [42]. (See the detailed description about the scale in the primary outcome part)

#### Exclusion criteria.

Exclusion criteria comprise pre-existing language barrier or aphasia caused by other disorders. History of other neurological diseases (e.g., cerebral small vessel disease, Alzheimer’s disease), mental illnesses (e.g., schizophrenia), other system diseases (e.g., hypothyroidism) which may cause cognitive impairments and consuming diseases or general poor health are further exclusion criteria for all participants. Furthermore, participants who are unable to cooperate in completing the assessment scales and have contraindications for rTMS therapy and MRI examination will not be recruited.

### Sample size

The sample size was estimated using G*power of 3.1.9.6 (www.gpower.hhu.de) [43–44], with the following parameters: effect size (*d*) = 0.86, α = 0.05 (two tails), power (1–β) = 90%, and allocation ratio n2/n1 = 1. The effect size was determined based on the result of our pilot study. The sample size in the current study should be 60 (30 in each group) after calculation. Considering a 10% dropout rate, a total of 66 patients are aimed to be recruited finally.

### Randomization and blinding

After obtaining informed consent, a random sequence will be generated by using the computer. A total of 66 participants will then be assigned randomly to the two groups (real or sham rTMS group) at a 1:1 ratio. Blinded grouping will be implemented using sealed envelopes with numbers. Both participants and the physiotherapists responsible for administering language rehabilitation training and rTMS therapy will be blinded to the treatment allocation.

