### Interventions

Participants will receive rTMS treatment by a same magnetic stimulator (model: YRD CCY-I, Wuhan Yiruide medical equipment New Technology Co., Ltd.). The targeted location is the right cerebellum, specifically 1 cm below the occipital tuberosity and 3 cm above the right paraspinal opening. rTMS treatment takes place at this spot utilizing an 8-shaped coil (9.2 cm in outer diameter), positioned fixedly and tangent to the scalp. The stimulation parameters include a frequency of 5 Hz, intensity set at 110% of the resting motor threshold (RMT) of the contralateral cerebral hemisphere, a duration of 5s, 25 pulses, a string interval of 20s, a session time of 20 min, 48 repetitions, totaling 1200 pulses [45–46]. In the sham stimulation group, the body surface positioning points and stimulation parameters are identical to those in the real rTMS group. However, the coil is positioned perpendicular to the scalp. Participants will receive treatments once a day for 20 minutes, five days a week, over a two-week period. Additionally, both groups will undergo conventional language rehabilitation training, with each session lasting 30 minutes and conducted twice a day.

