#### Primary outcome measurement.

The West Aphasia Battery (WAB) will be utilized to assess and monitor the improvement and deterioration of aphasia [42]. The assessment involves six language functions, which include spontaneous speech, auditory verbal comprehension, repetition, naming and word finding, reading, and writing. In the evaluation of aphasia, the AQ score is calculated to determine the severity of the condition. A higher AQ score indicates a milder form of aphasia and better language capabilities. The formula for calculating the AQ score is as follows: AQ = 2 × (spontaneous speech + auditory comprehension/20 + repetition/10 + naming/10). The total score is 100 points; higher scores suggest milder aphasia and improved language skills. AQ < 93.8 signifies aphasia.

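### The staff giving rTMS are said to be blinded, but the sham differs from real stimulation only by a visible coil orientation, so operator blinding cannot hold as written

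*Protocol article*

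**What the plan says.** All references are to the protocol article.

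- **Study design** gives the label: "This is a randomized, double-blinded, sham-controlled and single-center clinical study".
- **Randomization and blinding** says who is blinded: "Both participants and the physiotherapists responsible for administering language rehabilitation training and rTMS therapy will be blinded to the treatment allocation". No other role is listed.
- **Interventions** describes one device for everyone: "Participants will receive rTMS treatment by a same magnetic stimulator". In the real arm the coil is "positioned fixedly and tangent to the scalp". In the sham arm, "the body surface positioning points and stimulation parameters are identical to those in the real rTMS group", and the one stated difference follows: "However, the coil is positioned perpendicular to the scalp". Treatment is daily on five days a week for two weeks. Both groups also have two 30-minute language training sessions a day.
- **Primary outcome measurement** names the instrument: "The West Aphasia Battery (WAB) will be utilized to assess and monitor the improvement and deterioration of aphasia". Neither this section nor the one on secondary outcomes says who administers or scores the WAB or LOTCA.

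**The concern.** Two statements in the same article do not fit together. One says that the staff who administer rTMS do not know the allocation. The other separates the arms by something those staff would see, and describes nothing that hides it.

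The operator's knowledge matters because of where it could go. The blinding section uses one job title for the staff who give rTMS and those who give language training, and does not separate them. If they overlap, a person who knows the arm also delivers a co-intervention that acts directly on the primary outcome. Knowledge of the arm could also affect the rating of the WAB and LOTCA if anyone who has seen the stimulation is involved in scoring, and nothing in the text rules that out. Either route would tend to favour real rTMS in the primary comparison. Readers will also credit the trial with a level of masking that the described method cannot deliver.

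**Working it through.** **Step 1. Compare the arms feature by feature (Interventions).**

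| Feature | Real | Sham |
|---|---|---|
| Stimulator | same | same |
| Surface site | same | same |
| Stimulation parameters | same | same |
| Coil orientation | tangent | perpendicular |

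Orientation is the only stated difference, and it is visible to anyone at the coil. The article describes no sham coil, no coded device mode and no separate coil positioner. The schedule gives 5 days × 2 weeks = 10 sessions, each of which needs the coil in the orientation of the assigned arm.

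**Step 2. Set this against the blinding statement.** The statement covers the staff who administer rTMS. If those staff position or see the coil, they know the arm. The two sections can both be true only if something not described is added, such as a masking device or a separate positioner.

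**Step 3. Who else is covered.** Participants and therapists are named as blinded. The outcome assessor is not named, either as masked or as unmasked.

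**Step 4. The plan's own figure, for context.** Inputs from Sample size: d = 0.86, two-sided α = 0.05, power 90%, 1:1 allocation. The noncentral t calculation for a two-sample t-test gives 29.4, rounded up to 30 per group, with power 0.906 at 30. This reproduces the stated 60, and 60 × 1.10 = 66. No figure in the sample size is in dispute here.

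**Step 5. Illustration of what a bias would do.** The documents give no size for any bias, so the shift b (in SD of the outcome, favouring real rTMS) is an assumption. With no true effect and n = 30 per group, the test statistic follows a noncentral t with 58 degrees of freedom and noncentrality b × √(n/2) = b × √15 = 3.873b. The two-sided 5% rejection probabilities are:

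| Assumed b (SD) | Noncentrality | Rejection rate | b / 0.86 |
|---|---|---|---|
| 0.1 | 0.39 | 6.7% | 12% |
| 0.2 | 0.77 | 11.9% | 23% |
| 0.3 | 1.16 | 20.8% | 35% |
| 0.4 | 1.55 | 33.2% | 47% |
| 0.5 | 1.94 | 47.8% | 58% |

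The table shows what follows if a bias of that size exists. It is no evidence that one does.

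**The case against.** The strongest case on the other side has four parts.

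*Staffing is not described.* The article does not say who positions the coil. A separate positioner is neither described nor excluded, and the job title used in the blinding section fits one team or two. This stands as a limit: overlap between rTMS staff and SLT staff is possible, not shown. It does not rescue the blinding statement, which claims masking for the staff who administer rTMS without any means of achieving it.

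*Assessor masking may be in the full protocol.* A reader might infer that the WAB and LOTCA raters are unblinded. The article does not say so. It is silent, and a condensed article may leave this to a fuller document. What remains is narrower: the article does give a list of blinded parties, and that list omits the role that matters most for a rater-scored primary outcome. The right request is to specify it.

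*The Recruitment section.* It says: "The attending physician will collect data on medical history, neuroimaging, and scale assessment results". A reader might take this to mean that an unmasked physician scores the outcome. The sentence sits among recruitment arrangements and can be read as intake data, since eligibility itself needs a WAB score. It does not say who scores the follow-up visits or whether that person knows the arm, so nothing here rests on it.

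*The error rates are hypothetical.* Any assumed shift gives some inflated rate. This is correct, and the rates should not be used to judge how likely bias is.

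Nothing in this point contradicts the blinding of participants.

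**Conclusion.** The point holds in a limited form. As written, the blinding of the rTMS operator contradicts the described sham method, and the double-blind label fails so far as it depends on that blinding. This conclusion follows from the text alone and needs no assumption beyond the operator being able to see the coil.

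Two further matters are open, not established: whether the rTMS operator also delivers SLT, and whether the WAB and LOTCA assessors are masked. The documents support asking for both to be stated. They do not support saying that the SLT is contaminated or that the raters know the arm.

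The size of any resulting bias is unknown. The rates of about 12% and 21% depend on assumed shifts of 0.2 and 0.3 SD, no true effect and 30 analysed patients per group. They show only that a modest bias would matter in a trial of this size.

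**What to change.** 1. Reconcile Randomization and blinding with Interventions. Either list the rTMS operator as unblinded, or describe a sham set-up that does mask the operator.
2. State that anyone who positions the coil will not deliver SLT and will not administer or score the WAB or LOTCA.
3. Have the WAB and LOTCA at T1 to T4 scored by existing staff who do not attend stimulation sessions and are masked to allocation, and say so.
4. Restate in Study design and in Randomization and blinding exactly which roles are blinded, in place of the general label.

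The cost is some re-rostering and a label that reads slightly less favourably. The documents give no staffing numbers, so the ease of re-rostering is an assumption for the site to confirm. Trial status gives 1 June 2026 as the start of recruitment, so the change should be made as a dated amendment that also records how the patients already enrolled were treated and assessed. Sample size, endpoints and treatment schedule are unaffected.

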### Interventions

Participants will receive rTMS treatment by a same magnetic stimulator (model: YRD CCY-I, Wuhan Yiruide medical equipment New Technology Co., Ltd.). The targeted location is the right cerebellum, specifically 1 cm below the occipital tuberosity and 3 cm above the right paraspinal opening. rTMS treatment takes place at this spot utilizing an 8-shaped coil (9.2 cm in outer diameter), positioned fixedly and tangent to the scalp. The stimulation parameters include a frequency of 5 Hz, intensity set at 110% of the resting motor threshold (RMT) of the contralateral cerebral hemisphere, a duration of 5s, 25 pulses, a string interval of 20s, a session time of 20 min, 48 repetitions, totaling 1200 pulses [45–46]. In the sham stimulation group, the body surface positioning points and stimulation parameters are identical to those in the real rTMS group. However, the coil is positioned perpendicular to the scalp. Participants will receive treatments once a day for 20 minutes, five days a week, over a two-week period. Additionally, both groups will undergo conventional language rehabilitation training, with each session lasting 30 minutes and conducted twice a day.

### Outcome measurement

Outcome measures will be assessed across five time points: prior to rTMS treatment (T0), and at 2 weeks (T1), 3 months (T2), 6 months (T3), and 1 year (T4) post-treatment. The primary outcome is the evaluation of language function. Neuroimaging data, along with evaluations of non-linguistic cognitive functions, will serve as secondary outcome measures (Table 1).

**Table 1 pone.0354837.t001:** Outcome measures.

Outcome measures
**Primary outcome measures** ● WAB for determining the presence of aphasia and assessing language dysfunction recovery and deterioration.
**Secondary outcome measures** ● Imaging data for evaluating the structural, function and perfusion alterations in brain area. ● LOTCA for assessing nonverbal cognitive function.
**Safety outcome** ● Incidence of adverse events. ● VAS for assessing headache symptoms. ● FSAS for assessing fatigue symptoms.

Abbreviation: WAB: West Aphasia Battery; LOTCA: The Loewenstein Occupational Therapy Cognitive Assessment; VAS: Visual Analog Scale; FSAS: Fatigue Self-Assessment Scale.

